### Sample size

The sample size has been estimated from the primary outcome, peak oxygen consumption (VO_2peak_). A difference of 3.5 ml/kg/min in VO_2peak_ is regarded to be clinically relevant due to respectively 12–13 and 17% improvements in survival in men and women, with and without coronary heart disease [28–31]. The associated standard deviation was estimated to be 6 ml/kg/min based on the feasibility study conducted in the population [13]. This implies a moderate effect size (0.58). Given a power of 80% and level α = 0.05, a sample size of 47 in each group will be sufficient to detect a clinically relevant difference between groups. To allow for a 20% dropout, we aim at including 113 participants.

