**Methods:**

A protocol of a single-blinded, pragmatic randomized controlled trial. The study will take place in the eastern part of Norway, and will include heart patients who have completed CR. Participants will be recruited from two CR centers. Based on power calculation, 113 participants will be included. The intervention group will receive individualized follow-up through an app on a weekly basis throughout a year. The app will be set up with the participant’s own goals, and the follow-up will be based on these individual goals. The control group will receive usual care, including general advice regarding physical activity, exercise and diet. The participants will be assessed at baseline (at completion of CR) and 12 months after baseline. Primary outcome of the study will be peak oxygen uptake. Secondary outcomes include exercise performance, quality of life, health status, health literacy, self-perceived goal achievement, exercise habits, body weight, blood pressure as well as lipids and triglycerides.

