### Statistical procedures

The results of the study will be reported in accordance to CONSORT statement [27]. Statistical analysis will be performed using SPSS or a similar statistical package. Descriptive data will be reported for variables of interest and will be reported as mean (standard deviation), median (range) or numbers (percent) as appropriate. The data will be analyzed following the intention-to-treat principle. Prospective differences in primary and secondary outcomes and baseline characteristics between the intervention group and the control group will be assessed by t-tests for continuous and normally distributed variables and with non-parametric tests for categorical variables. To control for confounding of between group differences, multiple linear regression modelling will be used. We expect few or none missing data in baseline characteristics. However, due to possible dropouts or participants unable to complete some of the outcome measurements, there might be missing data for both primary and secondary outcome measures at follow-up. Missing data will be assessed and analyzed with appropriate methods. All tests will be two-sided. A plan for statistical analysis will be performed in advance of each paper from the study.

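### The target of 113 participants does not cover a 20% dropout from the required 94; it covers about 17% (minor correction)

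*Protocol article*

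**What the plan says.** All inputs are in the protocol article. Under Sample size, the target difference is given as "A difference of 3.5 ml/kg/min in VO_2peak_ is regarded to be clinically relevant", and the variability as "The associated standard deviation was estimated to be 6 ml/kg/min based on the feasibility study". The error rates follow: "Given a power of 80% and level α = 0.05". Statistical procedures adds "All tests will be two-sided", and the Randomization section sets 1:1 allocation. From these the plan concludes that "a sample size of 47 in each group will be sufficient to detect a clinically relevant difference between groups", which is 94 in total. The recruitment target comes next: "To allow for a 20% dropout, we aim at including 113 participants". The abstract repeats the number without a dropout rate or a power: "Based on power calculation, 113 participants will be included".

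**The concern.** A dropout rate is a share of those enrolled. A target that allows for 20% dropout should therefore still leave the required number once 20% of the enrolled participants are gone. Here 94 are required, but 113 less 20% is about 90.

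What is at stake is the accuracy of the sample size justification for the primary outcome. As written, a reader will believe that the trial keeps 80% power with one participant in five lost. Any dropout above 16.8% and up to 20% would lie within the declared allowance and still leave fewer than 94.

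**Working it through.** **Inputs** (Sample size, Statistical procedures and Randomization sections): difference 3.5 ml/kg/min; SD 6 ml/kg/min; two-sided alpha 0.05; power 80%; allocation 1:1; dropout 20%; 47 per group; target 113.

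**1. Reproduce the 47 per group.** The standardised difference is 3.5/6 = 0.583. The normal formula gives n = 2(1.960 + 0.842)²/0.583² = 46.1, rounded up to 47. The plan's figure is reproduced, and the evaluable total is 2 x 47 = 94. (A one-sided test would give 37, so the two-sided reading is the right one.)

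**2. Reproduce the 113.**
- Adding 20% to the evaluable number: 94 x 1.2 = 112.8, rounded to 113. This matches.
- Dividing by the retained share: 94/(1 − 0.20) = 117.5, rounded up to 118 (59 per group). This does not match.

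Of the two, only the multiplication returns the stated target.

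**3. What 113 leaves after 20% dropout.** 113 x 0.8 = 90.4, about 45 per group. That is roughly 4 fewer than 94 in total, or 2 per group.

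**4. What dropout 113 does cover.** 1 − 94/113 = 16.8%, which is 19 losses. A twentieth loss leaves 93.

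**5. Power at the numbers left.** For the normal approximation, power = Φ(3.5/(6√(2/n)) − 1.960). With n = 45 this is Φ(2.767 − 1.960) = Φ(0.807) = 79.0%. The t-test figures use the noncentral t distribution with 2n − 2 degrees of freedom.

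| Evaluable per group | Normal approximation | t-test |
|---|---|---|
| 47 (as required) | 80.7% | 79.9% |
| 45 (113 less 20%) | 79.0% | 78.1% |

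Within either method, the loss from 47 to 45 per group is 1.7 to 1.8 percentage points. On the t-test, the difference detectable with 80% power rises from about 3.50 to 3.58 ml/kg/min.

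**The case against.** The strongest reply is that the slip hardly matters, and much of that reply stands.

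- **Other uncertainty is larger.** The SD of 6 comes from a feasibility study of 14 patients. If all 14 contributed and the data are normal, its 95% interval runs from about 4.3 to 9.7. At 47 per group, t-test power would be about 92% with an SD of 5 and about 67% with an SD of 7. An SD of 5.86 instead of 6 would restore 80% at 45 per group.
- **Dropout may be lower than 20%.** The Discussion reports no dropouts in the feasibility study and describes retention measures. That study lasted only three months, however, and the same section names dropout as a particular worry. The 20% is the authors' own planning figure, so the target should be consistent with it.
- **The analysis may recover the loss.** The Discussion mentions mixed models and multiple imputation, and Statistical procedures mentions multiple linear regression. The sample size calculation takes no credit for any of these. Outcomes are assessed only at baseline and 12 months, so a participant who misses the 12-month test has no intermediate value to draw on. Adjusting for baseline could add precision, but the plan does not say whether the SD of 6 refers to the 12-month level or to the change. The gain cannot be sized from the document and should not be relied on.
- **The multiplication is inferred.** This is true. The conclusion does not depend on it, because 113 less 20% falls short of 94 however 113 was obtained.

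Stronger readings are tempting in the other direction. A reader might infer that 47 per group is itself wrong, since the t-test gives 79.9% there. It is the correct result of the normal formula, and the gap is a choice of method, not an error. A reader might also infer that the abstract is wrong. It states neither a dropout rate nor a power, and it stays true if 113 is kept.

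**Conclusion.** The dropout sentence in the Sample size section is wrong as written and needs a minor correction. Enrolling 113 covers 16.8% dropout from the required 94, not 20%. At 20% dropout about 90 remain, and power is 79.0% (normal approximation) or 78.1% (t-test), which is 1.0 to 1.9 points below the stated 80%. A target that does cover 20% would be 118, five more than planned.

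These figures rest on the plan's own difference, SD and alpha, on losses spread about evenly between the groups, and on an unadjusted comparison of means. A reader might go further and conclude that the trial is underpowered in a way that threatens its validity. The documents do not support that: the shortfall is about two evaluable participants per group, and neither the design nor the analysis is affected.

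**What to change.** Keep 113 and restate the sentence in the Sample size section in one of two ways:

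- 113 participants allow for about 17% dropout (16.8%) from the required 94; or
- with 20% dropout from 113, about 90 participants remain, and power for a difference of 3.5 ml/kg/min is about 78–79%.

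The cost is one sentence and a slightly less favourable statement of tolerated dropout or power. The abstract and the 47 per group can stay as they are. Raising the target to 118 would also make the present sentence true, at the cost of five more participants, but a loss of this size does not require it.

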## Discussion

To our knowledge, this will be the first study to examine the effects of one-year individualized follow-up with an app after completed CR, aiming to promote adherence to lifestyle advice. We anticipate that the intervention described will have a positive impact on the primary outcome, VO_2peak_, as well as secondary outcomes such as exercise performance, body weight, QoL and self-perceived goal achievement. If the intervention proves to be effective, we will be able to support participants in the intervention group to adhere to lifestyle advice and thereby maintain the beneficial effects they have achieved in CR, which has proven to be difficult for the patient population several times [5, 32, 33]. Additionally, by evaluating the impact of the intervention, we hope to contribute to fill the knowledge gap that has been addressed by previous research in the field [3, 6, 9, 12, 34], and it is reasonable to assume that the study may be groundbreaking. Due to the large sample size and the theoretically based intervention, the study has the potential to generate new knowledge that may improve the design of future technology-based follow-up interventions of patients that have completed rehabilitation.

The intervention to be evaluated in this study can be considered as a complex intervention, and therefore we will have a systematic approach as desirable in such interventions [35]. Methodological issues may influence the validity, and thereby influence the quality of the study. In the present study, we are particularly concerned with drop-outs and participants adherence to the intervention, which may threaten internal validity. Despite that there were no drop-outs in the feasibility study [13], we are not sure whether participants will participate in the described study for the whole period or whether they show up for the 12 months assessment. Results from our feasibility study [13] demonstrated high adherence to the app. However, participants in the feasibility study only received follow-up for three months. Results from a recent systematic review on physical activity apps on healthy individuals, shows more promising results on physical activity with an intervention duration of less than three months compared to interventions lasting more than three months [36]. Participants in the intervention group who don’t use the app for four weeks will be contacted through e-mail specifically in that regard. If a response is not received within a week, we will contact the participant by telephone. Regardless of whether one succeeds in achieving contact with the participant, the follow-up will take place as described, unless the participant has given notice that he or she wishes to withdraw from the entire study. At 12 months assessment, usage of the app, e.g. percentage of answered tasks over the study period, will be extracted through the administrator interface. This enables us to review the results against actual usage of the app. To increase the probability for participants to show up at 12 months assessment, a notice will be sent out about five weeks before. In addition, we will be as flexible as possible with respect to the day of the 12 months assessment. Hopefully, this will reduce drop-outs. Nevertheless, there is a risk for drop-outs and thereby missing data. Impact of missing data will be assessed with appropriate statistical methods, e.g. linear mixed models, multiple imputations and sensitivity analysis.

By following Medical Research Council’s framework in developing the complex intervention in this study, we believe that we have done what we can to increase the quality of the study. In this respect, a clear theoretical framework is of great importance [6, 35]. Additionally, techniques such as monitoring of specific and individual goals, individual feedback and identifying barriers and developing plans for relapse prevention will be used. These are techniques which has been demonstrated as the most effective in post-CR context to increase physical activity in cardiac patients [37].

If the intervention in the described study appears effective, one of its advantages is its applicability to other diseases or health challenges where adherence to a healthy lifestyle after rehabilitation is a challenge. Therefore, if the intervention proves to be effective, a plan for implementation will be addressed.

## Data Availability

Not applicable.

## Abbreviations

CR: Cardiac rehabilitation
CV: Cardiovascular
HR: Heart rate
QoL: Quality of life
RCT: Randomized controlled trial
